### Overall design of the competing risk models used to analyze time to discharge alive and to in-hospital death

The primary aim will be to analyze the association between daily propofol-associated energy intake from day 1 to day 11 after ICU admission and the time to the hospital endpoint (discharge alive with in-hospital death as a competing risk).

Recording of propofol-associated energy intake was stopped if a patient died, was discharged from the ICU, or was in the ICU for more than 11 days. However, our statistical model requires information on propofol-associated energy intake on propofol days 1 to 11 after ICU admission for all surviving patients, even if patients were discharged from the ICU before day 11. Assuming no propofol-associated energy intake after ICU discharge alive, we will impute a daily propofol-associated energy intake of 0 for these patients.

To account for the fact that a short duration of propofol therapy (and propofol-associated energy intake) may not affect outcome over a more extended period, we will use a lead-time defined as twice the number of days that a patient received propofol therapy. These lead times provide a window in which propofol-associated energy intake on a given day could have affected the subsequent day of discharge alive (time to discharge alive).

To facilitate the interpretation of the associations between propofol-associated energy intake and outcome estimated by our model, we will construct five different hypothetical propofol-associated energy intake use patterns (reflecting three different levels of daily propofol-associated energy intake (low, medium, high) on propofol days 1 to 11). These levels of use will also be used to model associations between propofol-associated energy intake and outcomes. Similar to our recent publications,^(9,15)^ we will distinguish between an early (days on propofol #0 to #4) and a late (days on propofol #5 to #11) acute phase.

We will then use these models to compare the expected outcomes of hypothetical propofol-associated energy intake patterns, controlling for confounders. We will design six different pairwise comparisons of these artificial patterns, analyzing the events of interest (separate models for early acute phase, late acute phase, or early + late acute phase: comparison of intermediate propofol-associated energy intake *versus* low propofol-associated energy intake, and high propofol-associated energy intake *versus* intermediate propofol-associated energy intake). All adjusted hazard ratios (pairwise comparisons of different hypothetical propofol-associated energy intake patterns) will be calculated assuming ceteris paribus.

The primary objective of the analysis of propofol-associated energy intake is to obtain the cumulative incidence function of the events of interest (time-to-discharge alive, taking into account the competing event of in-hospital death). We will again use PAMM. We will use techniques employed in previous publications^(9,15)^ to model cumulative effects where past values of a propofol-associated energy intake influence the hazard on a given day after ICU admission. This is relevant when accumulated propofol exposure may increase the risk of an event.

To model the cumulative effects over the follow-up period, we will use the lead time described above. This describes the time interval during which a propofol-associated energy intake registered on a given day after ICU admission affects the likelihood of hospital discharge alive or in-hospital death. We will first create the piecewise exponential data format by constructing covariate matrices for propofol-associated energy intake, additional matrices representing the time of exposure, and a lead matrix defining the time window during which the event of interest (hospital discharge alive or in-hospital death) will be recorded. Furthermore, we will divide the time axis after ICU admission into segments (Day x to Day x + 1 after ICU admission), assuming a constant exponential distribution within each segment.

Propofol-associated energy intake is a time-dependent covariate characterized by time-varying exposure. This time-varying exposure can be described by an individual's exposure history, in which a specific value of propofol-associated energy intake is attributed to each day after ICU admission. To model the cumulative associations, we will first compute the partial association over the time window containing the aforementioned segments, in which the value of propofol-associated energy intake on a given day after ICU admission can affect the hazard rates. For cumulation, we will use the weighted cumulative exposure model,^(28)^ in which the partial associations are assumed to be linear and depend only on the time window. This model is defined as the definite integral of the partial associations over the entire time window. Furthermore, the model computes the cumulative associations between time-varying propofol-associated energy intake and recency.

For the primary analysis, we will first fit cause-specific hazard models for each event type, and then combine the resulting models to estimate the cumulative incidence function for each event type.^(15)^ The cumulative incidence function is calculated by considering the probability of hospital discharge alive or in-hospital death until the end of the lead time. For comparison, we will also use the Fine–Gray subdistribution hazard model to analyze predictors (including the cumulative association of propofol-related energy intake) of time-to-discharge alive.^(29)^

The Fine-Gray model is a type of proportional hazards model used to estimate the probability of the event of interest (hospital discharge alive) occurring, while accounting for in-hospital death (a competing risk), which can prevent a patient from being discharged alive from the hospital. The Fine-Gray model directly estimates the cumulative incidence function of the cause of interest (discharge alive), and the advantage of this model is that the effects of covariates and exposures can be interpreted directly with respect to the cumulative incidence function. The general estimation approach will be equivalent to the cause-specific approach described above; however, there will be no need to model the competing event directly.

For time to discharge alive/in-hospital death, we will present adjusted hazard ratios (with 95%CIs) comparing two levels of cumulative propofol-associated energy intake. Adjusted hazard ratios will be calculated separately for each day after ICU admission in the defined time window. Cumulative incidence functions will show the estimated proportion (with 95%CIs) of patients who have been discharged from the hospital alive on a given day after ICU admission, by their cumulative propofol-associated energy intake.

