## METHODS

### Data base

The International Nutrition Survey is a multinational database of critically ill adults treated in 785 international medical, surgical, or trauma ICUs. This database includes, in addition to nutritional and outcome data, information on daily propofol use and associated fatty acid intake and has collected data on more than 20,000 critically ill patients. Details of this database have been presented in a previous publication, and to date, the results of 18 previous studies have been based on various subgroups included in this database. Details of these studies, which addressed various aspects related to medical nutrition therapy, can be found in the electronic database.^(9)^

The core of the present study will be the analysis of a subpopulation of this multinational database. Patients enrolled in this database were followed from the day of ICU admission. Nutritional and clinical parameters (including daily protein intake, lipid intake, use of MV, propofol, and propofol-associated fat energy intake (including soybean oil and purified egg phosphatide) were collected daily from Day 0 (day of ICU admission) until ICU discharge or death, or for a maximum of 12 days for patients still in the ICU. Survival was assessed until hospital discharge (dead or alive) up to 60 days from ICU admission. Only ICUs with at least one included patient were kept in the database.

During the ICU stay, patients received standard medical care (including MV and propofol) at the treating physician's clinical judgement. The principles of sedation, ventilation strategies, including lung protective ventilation, weaning, and prevention/therapy of ventilator-associated pneumonia, followed international guidelines in effect at the time of the data collection.^(10-13)^

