#### Data collection

Using a secure web-based data collection tool, the following information was collected: date of ICU admission, admission category (elective surgery, emergency surgery, and medical), primary admission diagnosis (nine categories), sex, age, BMI, daily use of MV/propofol therapy, and Apache II score on the day of admission. Attending physicians or allied healthcare professionals with expertise in nutrition practices (e.g., dietitians) also recorded daily protein intake and route of additional caloric intake (enteral nutrition, parenteral nutrition). For the first 11 days after ICU admission, the database contains information on protein and energy intake, as well as the number of days on which a patient received parenteral nutrition or oral feeding at any time.

Daily propofol-associated energy intake was also collected from the day of ICU admission (partial day) to a maximum of 11 additional days after admission. Information on the exact dose of propofol (administered via 1% or 2% solutions) was not available in the database. However, as propofol-associated energy intake is closely related to the dose of propofol, propofol-associated energy intake can be used as a surrogate parameter for this dose (1mL of a solution containing propofol contains 50mg of soybean oil, and 50mg of purified egg phosphatide, equivalent to 1.1kcal/mL).

Patients were followed in the hospital for a maximum of 60 days after ICU admission. We recorded the time to in-hospital death or discharge alive. Patients who remained alive in the hospital for more than 60 days were considered censored for both risks at that time.

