### Outcome measures

–**Primary outcomes:** time-to-hospital discharge-alive as a surrogate of morbidity, and to in-hospital death (adjusted hazard ratios and 95% confidence intervals [95%CI]).Adjusted hazard ratios compare two levels of daily propofol-associated energy intake. They will be calculated separately for each day after ICU admission using sub-distributional and cause-specific hazard models. The observation period will start on the day of ICU admission, and events (day of discharge alive/in-hospital death) will be registered from day 2 after ICU admission until the end of the lead-time (defined as twice the number of days that a patient received propofol therapy).–**Secondary outcomes:** the risk of state transition (adjusted hazard ratio and 95%CI) and the transition probabilities between the different states (Figure 1).State transition risks and probabilities will be referred to a certain amount of propofol-associated energy intake or a specific duration of propofol therapy; adjusted hazard ratios will be calculated for all 17 transitions (Figure 1). State transition will be registered until day 13 after ICU admission. Initial and absorbing states include "propofol: no/MV: no", "propofol: yes/MV: no", "propofol: no/MV: yes", "propofol: yes/MV: yes", post-transition absorbing states include "in-ICU death" and "ICU discharge alive.

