### Overall design of the multistate models

We will use multistate models to assess the association between cumulated daily propofol-associated energy intake preceding state transition; propofol-associated energy intake on transition day, and number of days with propofol therapy preceding state transition, adjusted for the use of MV, and the subsequent risk for an inevitable state transition (Figure 1).^(21,22)^ We will analyze state transitions on a daily basis (days 0 to 11 after ICU admission), since the database contains information on propofol use and total propofol-associated energy intake on a given day. There are no data on state transitions occurring within 24 hours. Furthermore, transitions between propofol states have only been recorded up to 12 days after ICU admission. This is because propofol data recording stopped if a patient died or was discharged from the ICU, or if they had been in the ICU for more than 11 days. In line with this, for the multistate models, we will only consider outcomes (absorbing states: in-ICU death and discharge from the ICU alive) up to day 12 after ICU admission.

All analyses (multistate models and competing risks, see below) will be performed using the Piecewise Exponential Additive Mixed Model (PAMM). Like the Cox model, this model class is a multiplicative hazards model that estimates the hazard rate (or, more generally, the transition hazards) conditional on the covariates. Coefficient estimates can be interpreted in the same way as in the Cox model, e.g., using hazard ratios. We will use the PAMM rather than the Cox model because it explicitly estimates the baseline hazard and facilitates the estimation of nonlinear and time-varying effects, as well as the inclusion of time-dependent covariates (e.g., the number of previous days on MV). The general idea is to partition the observation period into short time intervals and estimate a constant hazard rate for each interval. This enables the model to capture varying hazard rates at different times after ICU admission, making it suitable for situations where the risk of state transition changes over time (e.g., after ICU admission). In the context of a multistate model, the hazard by piecewise exponential models becomes the transition hazard. Details can be found in the references.^(9,15,23-26)^

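### Primary hazard ratios from about day 13 can attribute continuing, unrecorded propofol to recorded day 5–11 intake

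*Protocol article*

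**What the plan says.** All references are to the protocol article.

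- **Exposure recording.** Under Data collection, daily intake was collected "from the day of ICU admission (partial day) to a maximum of 11 additional days after admission". Under Data base, daily collection ran until ICU discharge or death, "or for a maximum of 12 days for patients still in the ICU". The section on the competing risk models says that recording "stopped if a patient died, was discharged from the ICU, or was in the ICU for more than 11 days".
- **Unrecorded days.** That section imputes zero intake after ICU discharge alive. It gives no rule for patients who are still in the ICU when recording stops.
- **Event window.** The same section says "we will use a lead-time defined as twice the number of days that a patient received propofol therapy". Under Outcome measures, observation starts on the day of ICU admission and primary events "will be registered from day 2 after ICU admission until the end of the lead-time".
- **Model and reporting.** A weighted cumulative exposure term is used, and "the model computes the cumulative associations between time-varying propofol-associated energy intake and recency". "Adjusted hazard ratios will be calculated separately for each day after ICU admission in the defined time window". Cumulative incidence is also carried to the end of the lead-time, and the pairwise contrasts are meant to hold all else equal.
- **Multistate models, for comparison.** Because recording stops, "we will only consider outcomes (absorbing states: in-ICU death and discharge from the ICU alive) up to day 12 after ICU admission".
- **Limitations.** The article acknowledges that propofol data end on day 11 and that associations refer to that period. It does not change the primary window or the daily hazard ratios in response.

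**The concern.** A recency-weighted term explains the hazard on a given day by intake on the days before it, with weights that depend on how long ago the intake was. This works while the preceding days are observed. For a patient who stays in the ICU on propofol beyond day 11, the most recent days drop out of the term from about event day 13, and only older intake remains. A patient's intake is likely to be correlated from day to day, so the recorded older intake can stand in for the unrecorded recent intake.

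Nothing else in the primary models is placed to absorb this. According to Table 1, they adjust for ventilation days on days 0 to 2, while the running ventilation count is used only in the multistate models.

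At stake is how the late-phase and early-plus-late contrasts are read. A hazard ratio on day 15, say, could be taken as a delayed effect of day 5–11 dosing when part of it reflects propofol still being given. A trend in the daily hazard ratios could arise partly from the stop in recording. The study wants to inform safe dosing and duration, and patients with long exposure are the ones who supply the estimates after day 12.

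**Working it through.** **The plan's own figure.** The only event count given is more than 10,000 discharges alive among more than 18,000 patients at about 70%. 18,000 × 0.70 = 12,600, which agrees. The point does not depend on it. Day 24 is not printed; it follows from the lead-time rule.

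**Step 1: length of the window.** Days 0 to 11 give at most 12 recorded propofol days. With n recorded propofol days, the window ends on day 2n, counted from ICU admission as under Outcome measures.

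| Recorded propofol days n | Window ends on day 2n | Event days after day 12 (2n − 12) |
|---|---|---|
| 6 | 12 | 0 |
| 7 | 14 | 2 |
| 9 | 18 | 6 |
| 12 | 24 | 12 |

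- The window passes day 12 only for n ≥ 7.
- The maximum is 2 × 12 = 24, or 2 × 11 = 22 if only days 1 to 11 count.
- The two-day lag analysis lowers these to 22 and 20. It supplies no intake for the days after day 11.
- Propofol days after day 11 are not counted in n, so the lead-time is itself capped by the recording stop.

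**Step 2: who is affected.** For an event on day 12, intake is recorded through day 11, the day before. For an event on day 13, intake on day 12 is unrecorded. Three groups separate:

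- Patients with n ≤ 6 have no event days after day 12.
- Patients discharged alive from the ICU by day 11 have zeros on a stated assumption.
- Patients with n ≥ 7 who are still in the ICU and still on propofol after day 11 have event days with recent intake missing. These are the affected patients.

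**Step 3: mechanism (illustration only).** Assume that the hazard depends only on the previous day's propofol, with true hazard ratio 0.7 and no carry-over. Assume also that a patient on propofol on day 11 continues from one day to the next with probability c, and that the comparison patients are off propofol from day 11 on. Ignoring selection by earlier events, the apparent hazard ratio of recorded day-11 intake on event day d is

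HR(d) = 1 − (1 − 0.7) × c^(d − 12).

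| c | Day 13: 1 − 0.3c | Day 16: 1 − 0.3c⁴ |
|---|---|---|
| 0.6 | 0.82 | 0.96 |
| 0.8 | 0.76 | 0.88 |
| 0.9 | 0.73 | 0.80 |

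The true direct effect of day-11 intake on these event days is 1.0. With a true hazard ratio of 1.5 instead, 1 + 0.5c^(d − 12) gives 1.30, 1.40 and 1.45 on day 13, and 1.06, 1.20 and 1.33 on day 16. Both sign and size therefore follow from the assumed effect and persistence, neither of which the article gives. The expected number of unrecorded propofol days over days 12 to 23, the sum of c^k for k = 1 to 12, is 1.5, 3.7 and 6.5 for the three values of c. This calculation does not fit the planned additive model; it shows only that recorded intake can carry the association of later intake.

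**The case against.** The best defence is that the exposure is defined as intake on days 1 to 11 and related to a later hospital outcome, which is a common and legitimate cohort design. Propofol after day 11 is then a consequence of earlier treatment, not an omitted covariate. The Limitations section also discloses the recording limit. This stands as far as the window goes: it need not be shortened. It does not cover the interpretation, because the article nowhere says that estimates after day 12 include later propofol. A recency-weighted model with all-else-equal contrasts and separate early and late phases invites the opposite reading.

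Three stronger readings are tempting and are not supported.

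- **The two model families contradict each other because only the multistate models stop at day 12.** In the multistate models, propofol yes or no defines the state, so no state exists without recording. The hospital outcome is followed to day 60. Different cut-offs are not in themselves an inconsistency.
- **The share of event days after day 12 measures the problem.** For propofol started on day 0, that share of days 2 to 2n is 4/15 = 27% for 8 propofol days and 8/19 = 42% for 10. Consecutive courses of that length end on day 7 and day 9, and non-use is then recorded through day 11. Such patients are affected only if propofol is restarted after day 11. These shares mostly restate the 2n rule.
- **The bias has a known size or sign.** The illustrations show mechanism only.

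It can also be said that a condensed article leaves the handling of individual cells in the lead matrix to a fuller plan. That is fair for coding detail. The article does, however, fix the window, the zero-intake rule and the daily hazard ratios, and the concern follows from those three.

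**Conclusion.** The concern holds in a limited form. For patients with at least 7 recorded propofol days who are still in the ICU and on propofol after day 11, primary hazard ratios from about day 13 (day 24 at most) cannot be read as recency-specific associations of recorded day 5–11 intake. They can include the association of continuing propofol that was not recorded.

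This rests on three conditions: some patients do continue propofol after day 11, intake is correlated from day to day, and recent intake is associated with the hazard. If any of these fails, the mechanism produces no misattribution. The article does not give the share still on propofol after day 11, so size and direction cannot be stated. The point bears on the late-phase and early-plus-late conclusions and on the cumulative incidence curves after day 12. Results up to day 12 are not affected by it.

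**What to change.** Keep the planned primary window and make two changes.

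1. Add a sensitivity analysis of the cause-specific and cumulative incidence models in which follow-up ends administratively at day 12 for all patients. Because the day is fixed, this censoring does not depend on the patient's course. Base statements about recency or about early- versus late-phase dose on results that agree with this run.
2. State that hazard ratios and cumulative incidence after day 12 are total associations of day 0–11 intake, including any propofol that continued unrecorded.

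An indicator for being in the ICU and on propofol on the last recorded day is not a good substitute. It largely duplicates the day-11 intake already in the exposure term, and it conditions on ICU status after exposure.

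The cost is some wording and one further set of model runs on existing data. In the sensitivity run there are fewer events and wider intervals. Late-phase intake also has little follow-up: 12 − 5 = 7 days for day-5 intake, down to 12 − 11 = 1 day for day-11 intake. Only patients with 7 to 12 recorded propofol days lose event days (2 to 12 each).

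### The Fine-Gray comparison uses time-varying propofol intake, an internal exposure, so its subdistribution hazard ratio for intake cannot be read directly on the cumulative incidence function as the protocol states

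*Protocol article*

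**What the plan says.** The section on the competing risk models describes the exposure this way: "Propofol-associated energy intake is a time-dependent covariate characterized by time-varying exposure". For the primary analysis it fits cause-specific hazard models for discharge alive and for in-hospital death and combines them into cumulative incidence functions. Then, for comparison, "we will also use the Fine–Gray subdistribution hazard model to analyze predictors (including the cumulative association of propofol-related energy intake) of time-to-discharge alive".

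Three statements about this second model matter here:

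- On interpretation: "the effects of covariates and exposures can be interpreted directly with respect to the cumulative incidence function".
- On fitting: "The general estimation approach will be equivalent to the cause-specific approach described above".
- On the competing event: "there will be no need to model the competing event directly".

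On the exposure data, the same section says that intake was no longer recorded once a patient had died, had left the ICU or had stayed there beyond day 11. Intake on days 1 to 11 is required for surviving patients. For those who left the ICU alive before day 11, "we will impute a daily propofol-associated energy intake of 0 for these patients". No rule is given for days after death.

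Under Outcome measures, the primary-outcome hazard ratios are to be calculated "using sub-distributional and cause-specific hazard models", with no ranking between the two.

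**The concern.** A Fine-Gray model for discharge alive does not remove patients who die. They remain in the risk set as people who can never be discharged. For a baseline covariate this does no harm, because the value is known for everyone, and the subdistribution hazard then maps one-to-one onto the cumulative incidence.

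Daily propofol intake is different. It is an internal covariate: its path exists only while the patient lives and is treated. After death there is no intake to enter, so the model cannot be fitted without an assigned value. No subdistribution hazard conditional on an exposure path that ends at death has the direct link to cumulative incidence that the protocol claims.

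At stake is how a published subdistribution hazard ratio for cumulated intake would be read. Part of any departure from 1 could come from the value given to dead patients. With more than 10,000 discharges expected, even a small artefact could carry a narrow confidence interval. A difference from the cause-specific result could also be mistaken for a real competing-risk effect.

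**Working it through.** **1. The protocol's own figure.** More than 18,000 patients with about 70% discharged alive gives 18,000 × 0.70 = 12,600. This agrees with the stated figure of more than 10,000 events. It bears on precision only; the point does not depend on it.

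**2. Who is affected.** Intake is recorded up to day 11. A patient who dies after day 11 has a complete history. A patient who dies before the end of day 11 has undefined intake on the remaining days. The zero-fill rule applies after ICU discharge alive and does not reach these patients. The cause-specific model does not need them after death; the Fine-Gray model does. The two fits therefore cannot simply be equivalent.

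**3. Why the assigned value matters.** Take one day and a binary intake level k (1 = on propofol, 0 = off). Let n_k be the living patients at risk, e_k the discharges, and d_k the earlier deaths assigned to level k.

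- Cause-specific hazard: e_k / n_k
- Subdistribution hazard: e_k / (n_k + d_k)

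If intake has no effect on discharge, e_1/n_1 = e_0/n_0 and the cause-specific ratio is 1. The subdistribution ratio is

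(1 + d_0/n_0) / (1 + d_1/n_1).

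- Zero after death: d_1 = 0, so the ratio is 1 + d_0/n_0, which exceeds 1 as soon as anyone has died.
- Last value carried forward: the ratio is below 1 whenever d_1/n_1 > d_0/n_0. This happens when propofol use falls over time among the living while the dead keep their last value.

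**4. Illustrative null simulation.** None of these inputs is in the document: 200,000 patients, discharge hazard 0.05 per day, binary current-day intake declining over time, intake unrelated to death or discharge, piecewise-exponential fit with day effects, no lead-time restriction.

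| Death hazard per day | Horizon (days) | Cause-specific HR | Subdistribution HR, zero after death | Subdistribution HR, last value carried forward |
|---|---|---|---|---|
| 0.01 | 11 | 1.013 | 1.078 | 0.986 |
| 0.02 | 11 | 1.003 | 1.129 | 0.954 |
| 0.03 | 11 | 0.997 | 1.185 | 0.930 |
| 0.01 | 22 | 0.997 | 1.123 | 0.949 |
| 0.02 | 22 | 0.998 | 1.239 | 0.912 |
| 0.03 | 22 | 0.986 | 1.321 | 0.877 |

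In the 22-day rows the simulated intake continues past day 11, which the real data do not record.

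**5. Cumulated intake and the lead time.** The protocol models cumulated intake and ends each patient's window at twice the number of propofol days. Two further null simulations used unweighted cumulated intake and death hazards of 0.008 to 0.02 per day.

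- Follow-up to day 23, no lead time: zero after death gave 1.06 to 1.13 per 30 kcal/kg; carrying the last level forward gave 1.01.
- Discharge hazard 0.05 per day and mean propofol duration of about 5 days: zero after death gave 1.03 to 1.09 with follow-up to day 22, and 1.01 to 1.03 once risk sets ended at the lead time. Carrying forward gave 0.97 to 0.99. Cause-specific ratios varied from 0.99 to 1.01.

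Zero-fill pushes the ratio above 1 in every set-up. The result under carry-forward depends on the set-up. The lead time shrinks the zero-fill distortion considerably.

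**The case against.** The strongest reply is that Fine-Gray is only a comparison. The analysis section makes the combined cause-specific models the primary route, and the stated primary objective, the cumulative incidence function, comes from them. This stands. A reader might infer that the primary analysis is invalid; it is not, because the dead leave the cause-specific risk sets. It does not remove the point. Outcome measures lists sub-distributional models among those giving the primary hazard ratios, and Limitations names both approaches as the way competing risks are handled.

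A second reply is that the value after death is a data-construction detail that an article may leave to a fuller plan or to the cited methods papers. That is fair for the missing rule alone. It does not rescue the interpretation sentence, which is incorrect for this exposure under any rule. Stating a rule would make the ratio reproducible, but the ratio would still depend on the rule.

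A reader might also infer that the protocol assigns zero intake to the dead and so biases the result towards faster discharge. No text says this; the zero rule is confined to patients discharged alive from the ICU.

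A third reply is that the simulated sizes do not match the planned model: three intake levels, a weighted cumulative exposure, hypothetical patterns and a patient-specific lead time. That also stands, so the figures show a mechanism and not an expected bias. The fixed hypothetical patterns do not repair the fit, however. They fix the path at prediction, while the coefficients still come from a risk set with undefined intake.

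**Conclusion.** The concern holds for the Fine-Gray comparison and for the sub-distributional hazard ratios listed under the primary outcomes. The claim of direct interpretation is correct for baseline covariates and wrong for time-varying intake. For deaths before the end of day 11 the model also lacks a defined exposure, so the cause-specific set-up cannot simply be carried over.

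The size in the real data cannot be derived from the document. Under assumed hazards and no true effect, the subdistribution ratio for current-day intake over 11 days lay between 0.93 and 1.19 depending only on the value given after death. For cumulated intake with risk sets ended at the lead time, zero-fill gave 1.01 to 1.03, close to the simulation noise. No particular bias should be quoted for this study. The primary cause-specific hazard models and the cumulative incidence functions derived from them are not affected.

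**What to change.** - **Outcome measures:** for the intake exposure, give cause-specific hazard ratios only, for discharge alive and for in-hospital death. Take the cumulative incidence of both events from the combined cause-specific models already planned.
- **Competing risk models section:** drop the Fine-Gray model for time-varying intake, and limit the sentence on direct interpretation to baseline covariates.
- **If a Fine-Gray comparison for intake is kept:** use an exposure fixed at a landmark, for example mean intake on days 0 to 4, among patients still alive and in hospital at the end of day 4. Label it supplementary. It excludes earlier events and does not address the late phase (days 5 to 11), so it cannot stand in for the planned early-plus-late contrasts.

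The cost is a wording change in two sections and one model fewer. What is lost is a single summary ratio on the subdistribution scale.
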